### Intervention

The “VR retrieval–TBS” intervention will be given twice within 1 week. Each intervention session contains a MA-related VR scene to retrieve memory (or a neutral VR scene in a control group), a 5-min TBS treatment, and a 10-min interval in between them to conform with the suggestion that a 10-min reconsolidation window may improve the effectiveness of the subsequent intervention (8, 57). A short TBS trial will be delivered before the full-length treatment to decrease risks and improve clinical adherence. The pulse intensity of TBS will be assigned according to identified individual resting motor threshold (RMT).

#### VR Retrieval

Two types of VR scenes containing a series of neutral or drug-cues respectively will be presented in this study. As introduced in our previous study (43), the VR neutral scene for VR interaction practice at the first time that the participants using VR devices will be, a room with a desk, two spheres, two cubes, two cylinders, a laptop, and a visual analog scale (VAS) presented on the wall of the room. The spheres, cubes and cylinders are interactive, which means they can be picked up or stacked in the VR environment using the handle. This scene for practice will be presented once for 5 min. Another neutral scene will be presented in the baseline test and post-test. The neutral scene will be presented for 3 min followed by MA scenes after a 1-min interval of darkness in between. This neutral scene is a room with a sofa, a coffee table, and a standing lamp. There are about 50 triangle, square, or cylindrical blocks on the coffee table, about 10 cm in diameter. All the blocks are interactive. There are two MA scenes. Both scenes will be presented in the baseline test and the post-test, each 3 min, with a 1-min interval in between. The first MA scene is a room with a sofa, a coffee table, a standing lamp, a wardrobe, and a cabinet. There are many items on the coffee table, including a small bag of MA, a roll of foil, a piece of foil, lighters, plastic beverage bottles, paper money, straws, tools for diluting and filtering MA (a beverage bottle with straws and filters), a cellphone and a laptop. A video of playing a card game is played on the laptop screen. There is a TV hanging on the wall, which can play dance music or gambling game videos through the VR handle. The second MA scene is a room with a bed, a coffee table, and a chair. The items on the coffee table are similar to those in the first MA scene. There is a male or female avatar on the bed doing a series of actions of taking MA. All sofas or beds in the virtual scene have seats of similar heights at the corresponding positions in the real room. The MA-related VR scenes that we would like to use have been validated for their effect on MA memory retrieval based on the data in our lab and previous studies (58). In the baseline test and post-test, after the three scenes (neutral, MA1, MA2), the VAS is presented on the wall of a room in VR. Two groups (MA VR scene + TBS, MA VR scene + sham TBS) will view either the first or second MA scene prior to TBS treatments. Another group (neutral VR scene + TBS) will view a neutral VR scene before TBS treatments. Each scene for memory retrieval will last 3 min at each treatment session with 1 min pre-dark and 1 min post-dark, ended by an embedded VAS for self-reported craving rating. Real-time EEG for brain activity will be recorded while the presentation of VR scene (see *Outcome Measures*).

All VR scenes will be displayed by HTC VIVE VR system containing a wired headset (110 degrees, 1,080 × 1,200, 90 Hz) and a wireless handle controller to provide participants with direct, realistic interactions. With a head-mounted display, participants wearing a headset will immerse into the VR scenes. The wireless controller will also be accessible for participants to interact with objects in the VR scenes and rate VAS. The VR scenes will be monitored by a care provider on a desk computer (Alienware 15-R2748, i7-7700HQ 16G 256GSSD+1T GTX1070 8G discrete graphics FHD). These VR scenes have been developed by our collaborative team with unity 3D and used in our previous study (43).

#### TBS Protocol

##### Target to Stimulate

Refer to related research and large-scale Magnetic Resonance Imaging/functional Magnetic Resonance Imaging (MRI/fMRI) data from https://neurosynth.org/, the OFC, functioning (including both orbital and media area) with encoding specific stimuli value (59, 60) has been located with an averaged MNI coordinates (-4, 36,−18). Following previous suggestion (61), the stimulated site targeting OFC will be located according to the standardized international EEG 10–20 position (Fp1). This brain area will be labeled on an EEG 10 - 20 system cap. The coil will be placed tangent to the scalp at the contact point (Figure 3). During the TBS or sham treatment, the TMS coil over Fp1 will be fixed by a holder on the coil's handle during the treatment. We will pause to adjust the position if there is any movement of the coil or head according to the participant's feedback.

**Figure 3 F3:**
[figure not shown]
The stimulation coil targeting Fp1 on EEG International 10–20 system positioning.

##### TBS Pattern

The cTBS will be applied to reduce activation of the OFC circuit. TBS sessions will be carried out with a hand-held figure-of-eight coil with the size of 90 mm diameter of one half of the “8” shape (B9076, Yiruide Co., Wuhan, China), attached to a YRD CCY-I stimulator (Yiruide Co., Wuhan, China). Following a 10-min rest after memory retrieval, participants either in the MA VR scene + TBS group (*n* = 15) or in the MA VR scene + sham TBS group (*n* = 15) or in the neutral VR scene + TBS group (*n* = 15) will receive two TBS sessions within 1 week. In each session, all participants will receive two 1,800-pulse trains of cTBS in 5 min (three pulses are given at 50 Hz as one burst; a burst will be given every 200 s as 5 Hz; one train for 120s, containing 1,800 pulses) with a pulse intensity of 80% of RMT following Hanlon et al. (62)'s suggestion. A 60-s break will give to participants after the first train (1,800 pulses). The choice of TBS intensity will consider the participants' real-time feedback and health condition to TMS stimuli. If a participant reported unbearable discomfort with TBS stimulation, we will turn down the intensity gradually until acceptable. If a participant still reported unbearable discomfort when the stimulation intensity was lower than 60% of the RMT, this participant will withdraw from the experiment. These parameters have been applied by previous studies (62) and proposed in safety guidelines (63).

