### Participants

Participants with MUD in Shanxi Drug Rehabilitation Center will be voluntarily recruited to this treatment. After initial confirmation, eligible participants will then be required to sign an informed consent. The number and reasons of exclusion individuals, as well as those who reject or withdraw consent will also be recorded. *Inclusion criteria:* Selected participants will have to (1) be clinically diagnosed with Amphetamine-Type Substance Use Disorder according to Diagnostic and Statistical Manual of Mental Disorders (DSM-5) criteria, (2) abstinence periods at least 2 weeks without obvious withdrawal symptoms (e.g., drowsiness and dysphoria), (3) be aged 18 and 45 years old, and be right-handed, (4) be able to speak and read Chinese, (5) sign a consent form before intervention procedure.

*Non-inclusion criteria:* Participants meeting at least one of the following criteria will not be enrolled in this study: (1) meeting the diagnostic criteria of any other psychiatric disorder under DSM-5; (2) using other kinds of drugs (e.g., heroin, cocaine) in the past 30 days; (3) having contraindications to TMS treatment (head trauma, epilepsy or the history of epilepsy, metal implant, pregnancy and so on); (4) having a history of mental illness or a family history of mental illness; (5) be insensitive to VR scene (identified at the baseline); (6) having received psycho-therapy or TMS intervention in the last 6 months; (7) receiving medication treatment recently; (8) illiteracy; (9) having visual or hearing problems; (10) the individual threshold of TMS was higher than 50% of the maximum output of the TMS equipment; (11) scheduled to receive psycho-therapy or medication treatment for the next 2 months. *Exit criteria:* Participants will be allowed to withdraw from the clinical trial if they (1) voluntarily wish to stop the TBS sessions; (2) can hardly tolerate any aversive reactions (e.g., itching, numbing) or have a desire for other treatments; (3) do not complete the TBS sessions for other reasons; (4) suffer from worsening symptoms such as enhanced craving.

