##### Sham TBS Protocol

The sham TBS treatment will be conducted with identical conditions of active TBS using a sham TBS coil. The sham coil has no difference in shape and appearance to that of the active coil except for an additional black coil sheath for reduction of the diffusion of magnetic fields. It delivers stimulation over only scalp skin and superficial muscles without proposed physiological modulation effects on the cortex (66).

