### Participant Timeline

All participants will be introduced to follow the schedule of baseline phase, treatment sessions and follow-up test. All patients passing the screening process will enter the treatment procedure. Participants will be grouped into A, B or C to receive MA-VR retrieval combined active TBS (MA VR-active TBS) or MA-VR retrieval combined sham TBS (MA VR-sham TBS) or neutral-VR retrieval combined active TBS (neutral VR-active TBS), respectively. The treatment includes two TMS intervention sessions within 1 week. Each session takes about 30 to 40 min including preparation time, VR retrieval of 3 min, relaxation of 10 min and continuous TBS of 5 min. The post-test will be conducted 1 to 4 days after the last session and the follow-up test will be taken over at least 1 month later. The timeline for participants in this trial is illustrated in Figure 2.

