#### Data Preparation and Descriptive Statistics

After inspecting original data, identifying unusual cases, transforming and summarizing data-sets according to different types of variables: the mean, median, standard deviation, ranges and valid samples will be required at first, as well as the counts and percentages specific for categorical variables. Firstly, running SPSS 21.0 for basic check of validated data both based on the extent of treatment completion (>85%) and accepted level of missing/obscure/contaminated data (<10–20%). The missing data will be estimated via multiple imputations. Secondly, the distribution of data will be analyzed both by stem-and-leaf plot (SPSS 21.0), the actual data calculated for normality overlay a normal curve will be required to determine that to what extent it is a normal distribution (without significance at given alpha = 0.05). For a poor fitted normal curve, non-parametric inferential will be selected, while the standard or similar standard alloy will run the parametric inferential.

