#### Identification Method and Management System

(1) above potential risks will be considered within exclusion criteria to select adequate participants at the screening stage. These criteria will be re-confirmed again before the delivery of stimulation;

(2) individualized parameters for treatment: the intensity will be identified as RMT according to the individual threshold, and it will be adjusted (80–110% RMT) based on the tolerance of each patient;

(3) if there is persistent pain, intolerable, or the participant subjectively requests to withdraw, the treatment shall not be continued and concomitant care will be offered.

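### A participant who cannot tolerate stimulation below 60% RMT must leave the experiment, so outcomes that need no stimulation, including the primary one, can be lost after randomisation

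*Protocol article*

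**What the plan says.** The TBS Pattern section of the protocol article sets the intensity at 80% RMT and lets it be lowered step by step for discomfort. If discomfort is still unbearable below 60% RMT, "this participant will withdraw from the experiment". The wording is mandatory and names the experiment, not the stimulation. It applies to people already placed in the three arms.

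Two other sections touch the same event:

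- The exit criteria under Participants are permissive: "Participants will be allowed to withdraw from the clinical trial if they (1) voluntarily wish to stop the TBS sessions". They also list intolerable reactions and incomplete TBS as grounds for leaving the trial.
- Identification Method and Management System says of persistent or intolerable pain, or a request to withdraw, that "the treatment shall not be continued and concomitant care will be offered". It does not mention later assessments.

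The primary outcome is the EEG response in VR at T0 compared with T3. T4 repeats it. Craving ratings, ECG and the anxiety, depression and mood questionnaires are collected at T0, T3 and T4. T3 is dated from treatment: "The post-test will be conducted 1 to 4 days after the last session". Data Preparation and Descriptive Statistics plans multiple imputation for missing data.

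**The concern.** Stopping a treatment and leaving a trial are different events. A participant who cannot bear the coil can still put on the headset, view the scenes, have EEG and ECG recorded and fill in questionnaires. The article fixes the opposite rule for this case, and no section says that someone who stops TBS is still assessed.

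The trigger is a reaction to the assigned coil. Groups A and C receive the active coil and group B the sham, which has a sheath to reduce the field. The chance of leaving could therefore differ between B and the other two arms, and the comparison of EEG change would then rest on a group selected after randomisation. With 15 per arm, and a calculated sample size equal to the planned enrolment, each person lost comes straight out of the number that the calculation required.

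**Working it through.** **1. What can be lost.** The T3 and T4 measures are EEG and ECG in VR, the craving VAS, SAS, SDS and POMS-SF. None involves TMS. All are at visits already scheduled.

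**2. How many.** The article gives no discomfort or withdrawal rate. Three features suggest few cases:

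- a tolerability run-in: "A short TBS trial will be delivered before the full-length treatment";
- the stepwise reduction in intensity;
- a screening limit that keeps out anyone for whom "the individual threshold of TMS was higher than 50% of the maximum output of the TMS equipment".

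With RMT at most 50% of output, 80% RMT is at most 0.80 × 50% = 40% of output, and the exit applies only below 0.60 × 50% = 30% of output. One to three losses in one arm is therefore an assumed range: 1/15 = 6.7%, 2/15 = 13.3% or 3/15 = 20% of that arm.

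**3. Reproducing the plan's sample size.** Inputs from Sample Size: f = 0.2496 as printed, k = 3 groups, m = 4 tests, α = 0.05, target power 0.95. Not stated, so assumed: correlation between repeated measures ρ = 0.5 and ε = 1 (sphericity). For the within × between interaction:

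- λ = f² × N × m / (1 − ρ)
- df1 = (k − 1)(m − 1), df2 = (N − k)(m − 1)

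At N = 45: λ = 0.0623 × 45 × 4 / 0.5 = 22.43, with df 6 and 126, giving power 0.955. This is the smallest N that reaches 0.95, so the stated 45 is reproduced.

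**4. The comparison actually at risk.** The section on inferential statistics analyses baseline versus post-test in three groups, a 3 × 2 design. With the same f, ρ and ε, m = 2 gives λ = f² × N × 2 / 0.5, df1 = 2 and df2 = N − 3:

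| Lost | N | λ | df | Power |
|---|---|---|---|---|
| 0 | 45 | 11.21 | 2, 42 | 0.832 |
| 1 | 44 | 10.96 | 2, 41 | 0.823 |
| 2 | 43 | 10.72 | 2, 40 | 0.813 |
| 3 | 42 | 10.47 | 2, 39 | 0.802 |

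Three losses cost 0.832 − 0.802 = 0.030. The formula treats the arms as equal in size, so it is approximate when all losses fall in one arm.

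**5. Precision of a two-arm contrast.** The standard error rises by the factor √(1/15 + 1/(15 − k)) / √(2/15), where k is now the number lost. This is 1.018, 1.038 and 1.061 for k = 1, 2 and 3, that is, about 2%, 4% and 6%.

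**6. Bias.** It is zero if leaving is unrelated to the EEG change. Otherwise its sign and size cannot be worked out from the document.

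**The case against.** The strongest reply is that the harm is read into a paragraph about delivering stimulation. The article nowhere says that T3 and T4 are refused, and follow-up of people who stop early is something an article may leave to the full protocol. The second half is fair for recording details and for how the treatment-completion check is used, and no point is made of those. It does not cover the exit rule itself, because the article states that rule and states it as leaving the experiment.

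A reader might infer that TBS Pattern and Identification Method and Management System contradict each other, one ending participation and the other only treatment. The documents do not support that. The second section is silent on assessments and handles stopping and asking to withdraw together. The exit criteria also treat intolerance as a ground for leaving the trial, though by permission.

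A reader might also compute a worst-case shift by removing the most extreme EEG responders from one arm. That assumes that nothing is imputed, whereas multiple imputation is planned. It also assumes a link between scalp discomfort and EEG change that nothing in the article shows. Nor is differential loss established: of the sham coil the article says "It delivers stimulation over only scalp skin and superficial muscles", so sham is not free of sensation, and A and C share the active coil.

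Imputation does help. However, for someone with no T3 record it rests on a model in place of a value that could have been observed, and it does not remove bias if leaving depends on the unseen outcome.

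Lastly, a full exit has a protective side. Participants are in compulsory rehabilitation, and T3 and T4 show drug scenes again. That argues for inviting people to these visits without requiring attendance.

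**Conclusion.** The point holds as a minor one. Followed literally, the 60% RMT rule gives up the primary outcome, and the secondary outcomes at T3 and T4, after randomisation and for a treatment-related reason, although the visits are scheduled and need no stimulation. The text does not say that these visits are refused; the loss follows only if the rule is applied as written.

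The precision cost is small: at most about 0.03 in power for the baseline versus post-test interaction with up to three losses, given f = 0.2496, ρ = 0.5 and ε = 1. The number of losses is assumed. Any bias is of unknown direction and size and may be nil. The reason to change the rule is that the loss is largely avoidable, not that it has been shown to be large.

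**What to change.** In TBS Pattern, replace the withdrawal clause with: *stimulation will be stopped; the participant will be invited to T3 and T4 and analysed in the assigned arm unless consent is withdrawn.* Add to the exit criteria under Participants that stopping TBS does not by itself end assessments. In Participant Timeline, date T3 from the planned second session for anyone who stops early, so that the visit has a defined date. Keep the 60% RMT stopping criterion.

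The cost is one sentence and two short clauses, with no new visits and no change to the sample size. The downside is that a few T3 and T4 values will reflect partial treatment and slightly dilute the estimated effect.

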##### Intensity Identification

The RMT is suggested as the minimal TMS intensity required to elicit motor evoked potentials (MEPs). It will be identified by flexion/extension movements of any finger, especially the index and little finger, in at least 5 of 10 consecutive MEPs trials (32). A single TMS session will be conducted by a figure-of-eight TMS coil following previous suggestions (64), with a gradual increase (5% each time) from 40% of median output intensity up to an intensity which could induce slight but significant finger movement. The coil will be applied over a suggested “finger motor cortex,” with a TMS-matched elastic cap. This location was examined about approximately 8–11 cm lateral and 0–4 cm anterior to the cranial vertex (65). Thus, the TMS provider should concern with both cap-provided “marker” and information about a relative position, to find the “hotspots” accurately.

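### The printed search for the resting motor threshold only rises from 40% in 5% steps, on a scale that does not match the eligibility cap, so it may overstate the threshold that sets the dose

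*Protocol article*

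**What the plan says.** In the protocol article, Intensity Identification gives the definition first: "The RMT is suggested as the minimal TMS intensity required to elicit motor evoked potentials (MEPs". The criterion is finger movement "in at least 5 of 10 consecutive MEPs trials". The next sentence describes the search, a "gradual increase (5% each time) from 40% of median output intensity up to an intensity which could induce slight but significant finger movement". The section then turns to coil placement. Neither it nor any other section mentions a start below 40%, a step down, or a finer final step.

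The stimulation levels are tied to this threshold:
- TBS Pattern sets treatment "with a pulse intensity of 80% of RMT". For discomfort, "we will turn down the intensity gradually until acceptable". A participant who still cannot tolerate stimulation below 60% of RMT is withdrawn.
- Identification Method and Management System says of the intensity that "it will be adjusted (80–110% RMT) based on the tolerance of each patient".

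The eligibility rule uses a different scale. Non-inclusion criterion 10 under Participants excludes a volunteer if "the individual threshold of TMS was higher than 50% of the maximum output of the TMS equipment".

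**The concern.** A minimal intensity has to be approached closely enough to tell it from the levels just below and just above. A search with a fixed start that only rises cannot return a value under its start, and a 5-point step cannot resolve a minimum that lies between steps. Both features push the recorded value up, so the printed search does not deliver the quantity that the same section defines.

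The scale is also unclear. *Median output intensity* is not defined, and the eligibility criterion uses maximum output.

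The stimulation levels are percentages of the recorded RMT, so an overstated RMT raises each of them by the same factor. The short trial stimulation, the turn-down and the stopping rule all respond to discomfort. None of them corrects the recorded threshold in a participant who tolerates the higher level. At stake are how accurately the dose is individualised and how far below threshold the nominal 80% level really lies.

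**Working it through.** The plan gives no figure for this point, so there is nothing to reproduce first. The check follows the printed search.

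**Inputs from the protocol article.** Start 40%, upward only, step 5% (Intensity Identification); dose 80% of RMT (TBS Pattern); cap at 50% of maximum output (Participants).

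**Assumptions.** (a) *Median* means maximum. (b) 5% means 5 points of output. (c) The level at which the ramp stops is recorded as the RMT.

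**Formulas.** Recorded RMT = first of 40, 45, 50, … at or above the true RMT. Delivered dose as % of true RMT = 80 × recorded / true.

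| True RMT | Recorded | Delivered, % of true RMT |
|---|---|---|
| 32 | 40 | 80 × 40/32 = 100.0 |
| 35 | 40 | 80 × 40/35 = 91.4 |
| 38 | 40 | 80 × 40/38 = 84.2 |
| 40, 45 or 50 | same | 80.0 |
| 41 | 45 | 80 × 45/41 = 87.8 |
| 46 | 50 | 80 × 50/46 = 87.0 |
| 48 | 50 | 80 × 50/48 = 83.3 |

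The upper limit between 40 and 50 is reached just above 40: 80 × 45/40 = 90, approached but not attained. If true values are spread evenly over 40 to 50, the mean is 80 × [45 ln(45/40) + 50 ln(50/45)] / 10 = 80 × (5.300 + 5.268) / 10 = 84.5%.

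**Chance in the 5-of-10 rule.** A simulation used a probit response curve with an assumed spread of 1 to 3 output points and true RMT uniform on 40 to 50. The mean overstatement was 2.1 to 2.4 points, the mean dose 83.8% to 84.3% of true RMT, and the recorded value was too high in 87% to 96% of participants. Chance sometimes stops the search slightly low, but the average error is still upward.

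**Other readings of the scale and step.**
- *Median* as half of maximum: the start is 0.40 × 50 = 20% and the step 0.05 × 50 = 2.5% of maximum. True values of 30 and 35 lie on a step and are recorded exactly. For 40 to 50 the limit is 80 × 42.5/40 = 85%.
- 5% as a relative step (40, 42, 44.1, …): above the floor the limit is 80 × 1.05 = 84%. Values below 40 are still recorded as 40.

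**The eligibility cap.** On the maximum reading, a true RMT of 50 is recorded as 50 and one of 50.1 as 55. The 50% cap therefore sorts volunteers correctly, chance aside.

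**The case against.** The strongest reply is that the article makes two separate statements. The RMT is identified by the minimal-intensity and 5-of-10 rule. The ramp sentence mentions neither the RMT nor recording its end point, and the text after it is about coil placement. The ramp could simply find a responsive site and level, with the threshold refined afterwards. On that reading neither the floor nor the rounding follows. The article also cites sources for the criterion and the procedure, and operators who follow them may refine anyway. This reading is possible, and it is why assumption (c) has to be stated. It is the less natural one, because the ramp appears under Intensity Identification directly after the RMT criterion and is the only search given. Nor is the point just a missing detail: start, direction and step are stated, and taken together they do not fit the definition.

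A reader might infer more than the text supports:
- *That the dose is shown to be too high.* It is not. The size depends on assumptions (a) to (c), and a true RMT exactly on a step is not overstated.
- *That participants may receive far more than 110% of threshold.* At the 110% end of the monitoring range, a true RMT of 35 would give 110 × 40/35 = 126%. That combines a low threshold of unknown frequency with an intensity above the 80% that TBS Pattern sets, a section that provides only for turning down.
- *That the raised 60% withdrawal limit adds risk.* A participant in discomfort would leave sooner, which is protective, although the limit is then not at its nominal level.

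**Conclusion.** The point holds in conditional form. As printed, the search does not match the definition of RMT beside it, and its scale does not match the eligibility criterion. If *median* means maximum, 5% means 5 points and the ramp's end point is the recorded RMT, the nominal 80% dose is 80% to just under 90% of true RMT for true values of 40 to 50, a typical drift of about 4.5 points. It rises below 40, to 91% at 35 and 100% at 32. The article gives no distribution of thresholds, so the share of participants below 40 is unknown and could be small.

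Most of these levels still lie within the 80–110% range that the article itself allows, so the typical effect is modest. It might be tempting to read this as a bias in the trial result, but the documents do not support that: the threshold procedure is common to all three arms, so the error favours none of them. The consequence is limited to dose accuracy and safety margin. This is a cheap improvement and does not threaten the trial's conclusions.

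**What to change.** In Intensity Identification, express the search in % of maximum stimulator output, the scale of non-inclusion criterion 10. State that the intensity is stepped down when the starting level already meets the 5-of-10 criterion. State also that the search finishes in steps of 1 to 2 points around threshold, and that the lowest level meeting the criterion is recorded as the RMT.

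For any true RMT of 30% or more, and before chance error, the nominal 80% dose then stays at or below 80 × 31/30 = 82.7% of true RMT with 1-point steps, or 80 × 32/30 = 85.3% with 2-point steps.

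The cost is a sentence or two of text and a few more single pulses per participant, with no extra equipment, staff or participants. If the operating procedure already works this way, only the wording of the section needs to change.
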